#### Statistical Analysis

To test whether dIST or even a single aIST session can accelerate postoperative respiratory and functional recovery, the primary analysis will compare between-group changes using a mixed-effects model to account for within-subject correlation in repeated measurements. Fixed main effects will include intervention and time; the participant will be included as the random effect. If baseline measures differ between groups, an analysis of covariance (ANCOVA) will be used. The primary analyses will be (1) change in MIP for dIST (vs other groups) from baseline to the preoperative assessment and (2) change in MIP from the preoperative assessment to the postoperative assessment for dIST and aIST (vs SOC). Holm adjustments will be applied for multiple comparisons.

Feasibility will be characterized by the percentage of completed dIST sessions, diary completion, and attrition rate. These will be reported as descriptive variables. The prevalence of PPCs will be compared between groups using chi-square or Fisher exact tests, as appropriate.

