### Participant Recruitment and Screening

Individuals with physician approval for elective joint replacement surgery who are interested in research participation will be referred to the study team by the Department of Orthopedics. We will enroll up to 60 participants. This includes 30% (18/60) participants who participated in nonrandomized, proof-of-principle pilot work for the purpose of estimating the sample size for the randomized study. Up to 70% (42/60) additional participants will be randomized, with the goal of completing procedures in 60% (36/60) randomized participants. The inclusion criteria are outlined in Textbox 1. Patients who meet the eligibility criteria and agree to participate in the study will sign a University of Florida Institutional Review Board (IRB)–approved informed consent form. The study coordinators will screen patients according to the inclusion and exclusion criteria via participant interview and medical record review.

Textbox 1.Inclusion and exclusion criteria for study participation.

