### Data Analysis

#### Sample Size Projection

The primary outcome measure is MIP. To project the sample size needed to detect changes in respiratory strength following dIST vs SOC, postoperative changes in MIP were obtained from a controlled, blinded study of IST in cardiac surgery [38]. Relative to baseline, postoperative MIP decreased by an average of 28 (SD 16) in the usual care group but only by 10 (SD 17) in the IST group. These data, along with similar publications of preoperative IST, demonstrate a moderate to large potential effect size to detect changes in MIP [22,24,26]. With a total of 36 participants (12 per group), a mixed-effects test could detect a 3×3 group-time interaction effect for training (partial η²=0.06, effect size (f)=0.253, α=0.05, 1−β=0.83).

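### Baseline adjustment of the primary MIP analysis depends on an undefined observed baseline difference; it should be fixed in advance

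*Protocol article*

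**What the plan says.** In the protocol article, Statistical Analysis, "the primary analysis will compare between-group changes using a mixed-effects model to account for within-subject correlation in repeated measurements". The model is described thus: "Fixed main effects will include intervention and time; the participant will be included as the random effect". The next sentence is the conditional rule: "If baseline measures differ between groups, an analysis of covariance (ANCOVA) will be used".

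Two primary contrasts in MIP follow. The first is "change in MIP for dIST (vs other groups) from baseline to the preoperative assessment". The second is the change from the preoperative to the postoperative assessment, comparing daily training (dIST) and the acute session (aIST) with standard of care (SOC). A Holm adjustment applies.

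Nothing elsewhere in the article commits to adjusting for baseline MIP. The Discussion mentions training volume and preoperative walking distance, but only as covariates to be explored. Under Outcomes, all groups have MIP measured at the baseline visit, in preoperative holding and 24 hours after surgery.

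**The concern.** The groups are randomised, so a baseline difference between them arises by chance. Observing one does not show that adjustment is needed, and failing to observe one does not show that it is unnecessary. The rule nevertheless lets that observation choose between two primary analyses. It leaves open which baseline measures are examined, what size or significance counts, and how ANCOVA relates to the mixed model.

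Two things are at stake. The first is prespecification: two analysts could follow the article faithfully and report different primary methods. The second is precision. With baseline as one of the repeated outcomes and group means left free, the mixed model's contrast of changes with complete data is simply the change-score contrast. When the rule does not trigger ANCOVA, the precision that baseline MIP could supply is not used, in a trial planned on 12 completers per group.

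**Working it through.** **Inputs.** From Sample Size Projection: 36 participants, 12 per group; "partial η²=0.06, effect size (f)=0.253, α=0.05, 1−β=0.83"; mean falls in MIP of 28 (SD 16) with usual care and 10 (SD 17) with training. The difference is 18 and the pooled SD is √[(16² + 17²)/2] = 16.5, a standardised change of 18/16.5 = 1.09. The correlation ρ between repeated MIP values is not given, so a range is shown.

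**1. The plan's own figure.** f = √(0.06/0.94) = 0.253. For the 3×3 interaction, λ = f²·N·m/(1−ρ) with N = 36, m = 3 and df 4 and 66. At ρ = 0.5, λ = 0.064 × 108/0.5 = 13.8 and power is 0.83, as stated. Power is 0.75 at ρ = 0.4 and 0.91 at ρ = 0.6. The stated power therefore fits ρ = 0.5, but the article does not say that this value was used.

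**2. How often the rule would trigger.** This depends entirely on what "differ" means.
- A 5% test on baseline MIP: 5% of trials.
- 5% tests on 3, 5 or 10 independent measures, any one triggering: 1 − 0.95^k = 14%, 23% or 40%.
- Any pairwise standardised difference above 0.1, 0.2 or 0.5, with 12 per arm: about 97%, 88% or 45%.

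**3. Precision for the baseline-to-preoperative contrast.** Per participant, the change score has variance 2σ²(1−ρ) and ANCOVA has σ²(1−ρ²). The ratio of ANCOVA to change score is (1+ρ)/2. The variance reduction forgone is (1−ρ)/2: 25% at ρ = 0.5, 15% at 0.7, 10% at 0.8 and 5% at 0.9.

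**4. Power for that contrast.** Simulation of 100,000 trials per setting: three arms of 12, dIST against SOC, standardised change 1.09, two-sided α = 0.05 without Holm. The rule is taken as ANCOVA only if the three-group baseline F test has p < 0.05.

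| ρ | Rule: power | Always ANCOVA: power | Rule: type I error |
|---|---|---|---|
| 0.5 | 0.744 | 0.838 | 0.045 |
| 0.7 | 0.739 | 0.790 | 0.046 |
| 0.8 | 0.738 | 0.767 | 0.048 |
| 0.9 | 0.736 | 0.746 | 0.049 |

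Repeat runs agree to within about 0.01. Type I error with ANCOVA always used was 0.050 throughout. If the first contrast means dIST against the other two groups pooled (12 against 24), rule against always ANCOVA is 0.856 against 0.927 at ρ = 0.5, 0.847 against 0.891 at 0.7, and 0.847 against 0.851 at 0.9.

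**5. The preoperative-to-postoperative contrast.** A random participant effect alone implies equal correlations. Then Cov(post − pre, enrolment) = ρσ² − ρσ² = 0, so enrolment MIP explains none of this change. Simulation (8,000 trials per setting) of change score against ANCOVA on enrolment MIP gives power 0.730 against 0.717 at ρ = 0.5, 0.740 against 0.728 at 0.7, and 0.732 against 0.716 at 0.9. There is no gain, and a small loss from the extra parameter.

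**The case against.** The strongest reply is that the article sets no 5% trigger. A reader might infer that the benefit of adjustment is lost in most realisations of the trial, but that follows only if a conventional significance test is meant. With a standardised-difference cut-off of 0.2, ANCOVA would be used in about 88% of trials. A condensed article may also leave the numerical criterion to a fuller document. This stands against the frequency claim. It does not rescue the rule, because no choice of threshold makes an observed chance difference a sound basis for selecting the primary method.

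A reader might also extend the power gain to the whole primary analysis. Step 5 shows that this fails for the second contrast under the plan's own random-effect structure. In a model of preoperative and 24-hour MIP with enrolment MIP as a main-effect covariate, that covariate cancels from the second contrast when data are complete. Using preoperative MIP as the covariate instead is no simple remedy: it is measured after dIST training, so conditioning on it could change what is estimated.

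The power figures are also illustrative. The 18 and 16.5 describe change from baseline to after cardiac surgery, which is neither primary contrast here, and the Holm adjustment is left out. These limits stand. They affect the size of the loss, not its direction for the first contrast.

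Finally, one might infer that choosing the model from the data produces false positives. The calculations do not support this: the rule is slightly conservative, and change scores are unbiased on average under randomisation. Regression to the mean matters only conditionally, in trials that happen to be imbalanced.

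**Conclusion.** The concern holds in a limited form. The article makes the primary method depend on an undefined observed baseline difference, and nowhere commits to using baseline MIP in every case. If the trigger is a 5% test on baseline MIP, the unadjusted change comparison is used in about 95% of trials. The cost for the pairwise baseline-to-preoperative contrast is then about 10 power points at ρ = 0.5, 5 at 0.7, 3 at 0.8 and 1 at 0.9. These figures rest on the assumed trigger, an unstated correlation, 12 per arm, unadjusted α and a borrowed effect size. No inflation of overall type I error was found, and no precision gain is claimed for the preoperative-to-postoperative contrast. This should be fixed because the remedy is free and settles the primary method in advance, but the trial's validity does not depend on it.

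**What to change.** Delete the conditional sentence. Prespecify, whatever imbalance is observed, one of two models for MIP:
- enrolment MIP as a covariate; or
- a constrained longitudinal model with a common baseline mean across groups and group-by-time terms.

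State that an observed baseline difference never triggers or removes adjustment, and that the covariate is enrolment MIP, not preoperative MIP. Claim the precision gain for the baseline-to-preoperative contrast only. Treat each spirometry outcome the same way, with its own enrolment value.

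The cost is a few sentences in the protocol or analysis plan. Baseline MIP is already part of the assessment schedule for all groups, so no new data or participants are needed. Since analysis is expected in 2027, the change should be made and dated before outcomes are examined by group.

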## Discussion

Despite strong evidence demonstrating the benefits of IST on respiratory strength, mobility, and PPCs after major cardiothoracic surgeries [21-24], little is known about its potential to offset surgical declines and accelerate recovery following TJA. This study focuses on TJA because of its high volume and expedited discharge pathway, with hospital lengths of stay averaging <1.5 days for total knee and hip surgeries [39] and anticipated to further decrease in the future [3]. Despite efforts to maximize efficiency of these surgical interventions, certain people with preexisting lung disease, multiple comorbidities, and frailty will require preemptive monitoring due to increased risk for complications. Preoperative IST is an inexpensive, nonpharmacological intervention with the potential to enhance preoperative readiness. As we cannot precisely control the exact timing and number of preoperative dIST sessions, the statistical analysis will explore the volume of dIST as a potential covariate of the primary study end points.

The inclusion of a single, intensive IST session in preoperative holding is a novel aspect of this study. Intense respiratory loading exercises induce temporary increases in respiratory neural drive that could potentially counter the reported decreases in diaphragm contractile function during controlled mechanical ventilation [29,30]. Although single exercise bouts are not expected to achieve lasting gains in function, even a temporary countermeasure may be advantageous for higher-risk surgical candidates who lack the ability to complete weeks of preparatory exercise, whether due to a lack of transportation to attend appointments, challenges with health literacy, or the need for an unplanned or emergent surgery.

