The primary outcome of this trial is MIP, a clinical estimate of strength. However, additional secondary measures were included to investigate the effects of the interventions on early postoperative activity-based measures such as coughing force, walking distance, and functional mobility, along with patient-reported dyspnea. Postoperative walking and functional mobility are important functional limitations following TJA that influence the timing of disposition and postacute rehabilitation needs [40]. Although the projected effect size of preoperative IST appears robust for impairment-level outcomes, this study will also provide early indication of its ability to carry over to functional activities and participation-level recovery. As preoperative 6MWD can predict functional ambulation after total joint surgeries [41], the statistical plan will explore preoperative walking distance as a covariate.

As a first preliminary study in TJA, some aspects of the study design remain limited. The sample size was projected from published work in cardiac surgery to detect changes in MIP between dIST and no preoperative exercise. Although we anticipate gaining valuable feasibility information regarding completion of aIST in the acute preoperative setting, we may lack the power to comprehensively distinguish which preoperative training approach (dIST or a single aIST session) can more effectively retain postoperative MIP and functional mobility. Postoperative walking and functional mobility at 24 hours can be influenced by a multitude of factors beyond respiratory strength and may include variations in pain management and pain perception, the ability to participate in same-day therapy, and lack of sleep, nutrition, or hydration. Blinded evaluators will plan for premedication with nursing before the planned 24-hour PT session and ensure that the timing does not interfere with meals. Participants randomized to SOC did not receive a respiratory trainer or training diary or undergo weekly check-ins, and the absence of a sham or attentional control group could inadvertently introduce expectation bias. Even in higher-risk patients, there may be few PPCs in the 30-day period following TJA. However, monitoring complications will enable us to further explore the prevalence of postoperative pulmonary issues in this cohort. Surgeons and study evaluators will be blinded to group assignment, but patients and other study staff will, by necessity, know the allocation.

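### The stated power of 0.83 belongs to the omnibus group-time interaction, not to the Holm-adjusted primary contrasts, and the low-power caveat leaves out aIST vs SOC

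*Protocol article*

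**What the plan says.** All references are to the protocol article.

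- **Sample Size Projection, purpose.** The section opens "To project the sample size needed to detect changes in respiratory strength following dIST vs SOC". Its one set of group figures comes from a cardiac surgery study: "Relative to baseline, postoperative MIP decreased by an average of 28 (SD 16) in the usual care group but only by 10 (SD 17") with IST. It also cites similar publications as showing a moderate to large effect.
- **Sample Size Projection, power.** The planned size is given as "With a total of 36 participants (12 per group"). The power claim for that size is that "a mixed-effects test could detect a 3×3 group-time interaction effect for training", and its inputs are listed as "partial η²=0.06, effect size (f)=0.253, α=0.05, 1−β=0.83". The within-person correlation is not given.
- **Statistical Analysis.** Primary analysis 1 is the MIP change from baseline to the preoperative assessment, dIST against the other groups. Primary analysis 2 is "change in MIP from the preoperative assessment to the postoperative assessment for dIST and aIST (vs SOC"). Holm adjustment applies; the number of comparisons in the family is not given.
- **Discussion, limitations.** The article says that sizing was for dIST against no preoperative exercise. It then adds that "we may lack the power to comprehensively distinguish which preoperative training approach (dIST or a single aIST session) can more effectively retain postoperative MIP".

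**The concern.** Three parts of the article do not fit together.

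1. **Test.** The powered test is an interaction with 4 numerator degrees of freedom. The primary tests are separate contrasts, each at a Holm-adjusted level.
2. **Interval.** The 18-point difference runs from baseline to after surgery. The primary contrasts split that span at the day of surgery. The MIP section places baseline about 4 weeks before surgery. On that meaning the 18 points are shared between the two primary intervals, and the shares are not stated. If the cited study's baseline was instead just before surgery, the figure fits dIST vs SOC in analysis 2, and analysis 1 has no planning effect.
3. **Arm.** On either reading, no effect is given for aIST vs SOC, although it is a primary comparison. The limitation on power names a different comparison, dIST against aIST.

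The risk lies in interpretation. Aim 2 asks whether a single session attenuates the postoperative fall in MIP. A non-significant aIST vs SOC result could be read as a negative from an adequately powered comparison, which nothing in the article supports.

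**Working it through.** **Inputs from the article:** 36 participants, 12 per group; three groups and three times; f=0.253; α=0.05; falls of 28 (SD 16) and 10 (SD 17). No unit is given, so the differences are called points here.

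**Assumptions:** within-person correlation ρ; SD 16.5 for each primary change, borrowed from the longer interval, with SD 10 as an alternative; a Holm family of three or four contrasts. It is four if dIST is compared with aIST and with SOC separately in analysis 1, and three if those two groups are pooled. The first Holm step is 0.05/3 = 0.0167 or 0.05/4 = 0.0125.

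**Step 1: the article's own figure.** f = √(0.06/0.94) = 0.2526, consistent with 0.253. For the within-between interaction, λ = f²·N·m/(1−ρ), with df (3−1)(3−1) = 4 and (36−3)(3−1) = 66. At ρ=0.5, λ = 0.0640×36×3/0.5 = 13.8, and power is 0.83. The stated figure reproduces. It depends on ρ: power is 0.67 at ρ=0.3, 0.75 at 0.4 and 0.91 at 0.6.

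**Step 2: the planning difference on one contrast.** Pooled SD = √((16²+17²)/2) = 16.51. Standardized difference = (28−10)/16.51 = 1.09. For 12 vs 12, the noncentrality is 1.09×√(12/2) = 2.67 with 22 df (noncentral t, two-sided).

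| Level | Power, full 18 points | Power, 9 points |
|---|---|---|
| 0.05 | 0.72 | 0.25 |
| 0.0167 | 0.54 | 0.13 |
| 0.0125 | 0.49 | 0.11 |

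With 66 df pooled from the model, the middle column becomes 0.75, 0.59 and 0.54. The 9-point column illustrates an even split of the 18 points over the two intervals; the article states no split.

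**Step 3: detectable difference at 80% power.** For 12 vs 12, the required standardized difference is 1.197, 1.414 and 1.469 at the three levels. Multiply by the SD:

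| Level | 12 vs 12, SD 16.5 | 12 vs 12, SD 10 | 12 vs 24 pooled, SD 16.5 |
|---|---|---|---|
| 0.05 | 19.8 | 12.0 | 16.8 |
| 0.0167 | 23.3 | 14.1 | 19.7 |
| 0.0125 | 24.2 | 14.7 | not applicable |

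The last column applies only to analysis 1, if dIST is compared with the other two groups combined. The family is then three, so 0.0125 does not arise.

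**Step 4: aIST vs SOC.** There is no assumed effect to put in. What can be said is the detectable difference for 12 vs 12 in Step 3.

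**The case against.** The strongest reply is that the article claims no more than it shows. It labels 0.83 as the power of the interaction. The formal input is f=0.253, which covers all three arms and times, and further cited studies support the effect size. The Discussion says openly that sizing was for dIST against no exercise, and it calls the trial a first preliminary study. All of this stands. The 0.83 is not wrong, and a careful reader could infer that aIST vs SOC was not the sizing contrast. But the interaction power still does not describe the contrasts declared primary, and the one comparison named as weak is not aIST vs SOC.

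Four stronger readings are tempting and are not supported.

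- **The planning effect matches no primary comparison at all.** This depends on what baseline meant in the cited study. If it was just before surgery, dIST vs SOC in analysis 2 is covered.
- **Every primary contrast needs about 20 points.** This fails if analysis 1 pools the other groups (16.8 at α=0.05), or if the SD of the shorter changes is nearer 10.
- **The authors expect no aIST effect.** The Discussion does say that "single exercise bouts are not expected to achieve lasting gains in function", but the same sentence argues that a temporary countermeasure may help, and the Introduction hypothesizes that short-term potentiation attenuates the postoperative fall.
- **aIST vs SOC should leave the Holm family.** It is central to aim 2. Demoting it during enrolment is a trade-off that low power alone does not require.

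**Conclusion.** The concern holds as a mismatch between the stated power and the declared primary analyses, together with a power limitation that is too narrow. The 0.83 applies to the omnibus interaction at a correlation of about 0.5. On a 12 vs 12 contrast, even the whole 18-point planning difference has power of about 0.72 unadjusted and 0.49 to 0.54 at the first Holm step (22 df). These figures assume that SD 16.5 holds for each primary change, and the adjusted ones assume a family of four or three.

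The most favourable reading is dIST against both other groups pooled with all 18 points falling before surgery. Its detectable difference is 16.8 unadjusted, below 18, but 19.7 at the first Holm step, above it.

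Two conclusions do not depend on the SD or the family size: aIST vs SOC has no planning effect, and the effect for analysis 1 is unquantified, either wholly or as an unstated share of the 18 points. The point should be addressed. It does not invalidate the design or call for a larger sample.

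**What to change.** **Sample Size Projection.** State that 0.83 applies only to the omnibus 3×3 interaction, and give the correlation assumed. Then give power or detectable difference for each primary contrast, with the SD, the number of comparisons in the Holm family, and whether the other groups are pooled in analysis 1. The Step 3 figures can serve if the SD is marked as an assumption. State also what baseline means in the cited study.

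**Discussion, limitations.** Extend the power caveat to aIST vs SOC and to the individual primary contrasts. Say that a non-significant aIST vs SOC result will be interpreted from its estimate and 95% confidence interval, not as a powered negative.

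**Keep** aIST vs SOC in the primary family.

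**Cost.** A few sentences in the protocol or analysis plan, with no change to sample size, conduct or primary outcome. The published power statement becomes less favourable. With analysis expected in 2027, the wording can be settled before results are known.

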## Methods

### Trial Design

This is a randomized, prospective, single-blind clinical study. Eligible participants will be randomized to one of three study groups: (1) dIST, consisting of IST 5 days per week for a period of 2 to 4 weeks before surgery; (2) aIST, consisting of a single aIST session delivered just prior to surgery; or (3) standard of care (SOC), consisting of usual preoperative, surgical, and postoperative care. Participants will be tested at established time points beginning with a baseline preoperative visit approximately 1 month before surgery and will participate in tests through 24 hours following surgery. PPCs will be monitored for 30 days. This study is registered on ClinicalTrials.gov (NCT5381818), and trial reporting will be guided by the SPIRIT (Standard Protocol Items: Recommendations for Interventional Trials; Checklist 1) and CONSORT (Consolidated Standards of Reporting Trials; Checklist 2) procedures (Figure 1) [33]. Proof-of-concept data were collected with support from an internal pilot grant award, and the controlled study is being conducted with funding from the National Institute on Aging (NIA; R21 AG083667).

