##### MIP

MIP is the primary outcome measure and represents the most negative pressure achieved by a participant during a maximal static inspiratory effort. Participants will be tested in accordance with American Thoracic Society (ATS) guidelines. MIP will be tested at the baseline assessment (approximately 4 weeks before surgery), in preoperative holding, and 24 hours postoperatively. Trials will be administered until a 10% variability is achieved across 3 trials (usually within 5 trials).

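### For aIST vs SOC, primary contrast 2 starts from the preoperative MIP alone, so the enrolment MIP, also untreated in both arms, is left out of the estimate and some precision is lost

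*Protocol article*

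**What the plan says.** Trial Design describes the acute arm as "aIST, consisting of a single aIST session delivered just prior to surgery". The aIST section places that session within 30 minutes of anesthesia induction. The SOC section includes no inspiratory training.

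The MIP section sets the same schedule for every group: "MIP will be tested at the baseline assessment (approximately 4 weeks before surgery), in preoperative holding, and 24 hours postoperatively".

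Statistical Analysis names two primary analyses of MIP. The first compares dIST with the other groups from baseline to the preoperative assessment. The second is "change in MIP from the preoperative assessment to the postoperative assessment for dIST and aIST (vs SOC"). The model is a mixed model with intervention and time as fixed effects and participant as the random effect. ANCOVA is used only if baseline measures differ between groups, and its covariate is not named. Holm adjustment is applied.

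The sample size is "With a total of 36 participants (12 per group"). Its power statement is for the overall group-by-time interaction, not for aIST vs SOC.

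**The concern.** Until the acute session, aIST and SOC receive the same care. Their enrolment and preoperative MIP are therefore both pretreatment measurements, provided that the preoperative test precedes the session. MIP depends on effort, and a single test is noisy. A contrast that subtracts one pretreatment test carries all of that test's noise, although a second pretreatment test has been collected in both arms.

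The comparison is a primary one, has 12 per arm and has no power figure of its own. Precision that costs nothing to collect is worth having here. The point does not extend to dIST, whose preoperative value comes after training.

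**Working it through.** **1. The plan's own figure.** The plan says 36 participants "could detect a 3×3 group-time interaction effect for training" with "effect size (f)=0.253, α=0.05, 1−β=0.83". The noncentral F test uses λ = f²·N·m/(1−ρ) with N = 36, m = 3 and an assumed ρ = 0.5: 0.253² × 36 × 3 / 0.5 = 13.83. With 4 and 66 degrees of freedom, power is 0.833. The stated 0.83 reproduces. It says nothing about aIST vs SOC alone.

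**2. Does the three-time-point model use the enrolment MIP anyway?** A random-intercept model with group-by-time means was fitted to three simulated complete data sets. The aIST vs SOC estimate for contrast 2 was 7.851, 2.234 and 10.723, identical each time to the plain difference in postoperative minus preoperative change. When only the enrolment values were altered, the estimates stayed the same. The standard errors moved, through the pooled residual variance. So the enrolment MIP informs the variance estimate but not the point estimate.

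**3. Variance of the alternatives.** Let b, p and o be the baseline, preoperative and postoperative MIP, with equal variances σ². In units of 2σ²/n per contrast:

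- planned change: 2(1 − r_po)
- change from the average of b and p: 1 + (1 + r_bp)/2 − r_bo − r_po
- regression on p only: (1 − r_po²)(1 + 1/20)
- regression on b and p: (1 − R²)(1 + 2/19), where R² = (r_bo² + r_po² − 2·r_bp·r_bo·r_po)/(1 − r_bp²)

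The factors 1/20 and 2/19 are the price of estimating slopes from 24 participants: 24 − 2 − 1 − 1 = 20 and 24 − 2 − 2 − 1 = 19.

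Example with all correlations 0.5: the planned change gives 1.00. Regression on both has R² = (0.25 + 0.25 − 0.25)/0.75 = 0.333, so 0.667 × 1.105 = 0.737, a saving of 26%.

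The documents give no correlations, so all of these are assumed. Variance relative to the planned change:

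| r_bp / r_po / r_bo | Average of two | Regression on p only | Regression on both |
|---|---|---|---|
| 0.5 / 0.5 / 0.5 | 0.75 | 0.79 | 0.74 |
| 0.7 / 0.7 / 0.7 | 0.75 | 0.89 | 0.78 |
| 0.9 / 0.9 / 0.9 | 0.75 | 1.00 | 0.81 |
| 0.7 / 0.6 / 0.5 | 0.94 | 0.84 | 0.87 |
| 0.8 / 0.7 / 0.5 | 1.17 | 0.89 | 0.92 |
| 0.8 / 0.8 / 0.64 | 1.15 | 0.95 | 0.99 |
| 0.9 / 0.9 / 0.81 | 1.20 | 1.00 | 1.05 |

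Simulation at 12 per arm agrees to within about 1 percentage point; the last entry came out at 1.06. Over the unequal sets simulated, regression on both ran from about 14% saved to 6% lost. These sets are examples, not bounds.

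**4. Where the gain comes from.** At equal correlation 0.5, regression on the preoperative value alone already saves 21% of the 26%. At 0.9 it saves nothing, and the whole 19% comes from the enrolment value. In the four unequal sets, the enrolment value adds nothing beyond the preoperative one and costs about 3% to 5%.

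**The case against.** The planned contrast is valid, unbiased and matched to aim 2, which asks about attenuating the postoperative decline. A better covariate set could be seen as detail for an analysis plan that is not shown. That is fair as to severity. But the article itself names this primary contrast and its starting value, and brings in ANCOVA only when groups happen to differ, so the point concerns what is stated.

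The gain may also be small. Baseline is typically 4 to 6 weeks before surgery and the preoperative test is on the day, so the enrolment MIP may well correlate less with the postoperative value. A random intercept is a modelling choice, not evidence of equal correlation. This stands, and it is why the lower rows of the table matter.

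The order of testing and training in preoperative holding is not written down. It is implied, because the first primary analysis groups aIST with the comparators at that visit and the second uses the visit as the aIST starting point. If the test came after the session, the adjustment would be for a treated value, and the planned contrast would have the same flaw.

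The preoperative MIP is also measured after randomization, in participants who know their group, and depends on effort. Equal means there are not guaranteed by randomization. The planned contrast already carries that weakness.

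**Conclusion.** The point holds as a modest loss of precision. The saving from regression on both values is about 19% to 26% of the variance if correlations are equal (0.9 to 0.5). It falls to between 14% saved and 6% lost in the sets tried where the enrolment value correlates less with the postoperative value or the two pretreatment values are very highly correlated. The result rests on 12 completers per arm, equal variances, assumed correlations and a preoperative MIP taken before the session.

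Three stronger readings are not supported:

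- **Bias.** Nothing here makes the planned estimate wrong on average. Nor is the enrolment MIP thrown away altogether: it stays in the model and the variance estimate, and could enter through the conditional ANCOVA.
- **A flat 25% saving, as if 16 rather than 12 per arm, with power rising from 0.72 to 0.84.** Those figures belong to change from the simple average under equal correlation, not to the regression. The average can be up to about 20% worse than the plan (last row of the table). The power figures also borrow a standardized effect of 18/16.5 = 1.09 from "postoperative MIP decreased by an average of 28 (SD 16) in the usual care group but only by 10 (SD 17) in the IST group". That is a cardiac-surgery result, from baseline to after surgery, used in the article for dIST vs SOC. The Discussion does not expect lasting gains from a single bout. The figures also leave out Holm.
- **A remedy for dIST vs SOC.** For dIST only the enrolment value is untreated.

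**What to change.** For aIST vs SOC only, prespecify the primary estimate as the group difference in postoperative MIP from a regression on both the baseline and the preoperative MIP, applied whether or not the groups differ at baseline. Do not use change from the simple average of the two. State that the preoperative MIP is recorded before the aIST session.

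The cost is a few sentences and no new data; analysis is not expected until 2027. There are four downsides to state:

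- One more slope is estimated than with adjustment for the preoperative value alone, which can cost a few percent of variance if the enrolment value adds nothing.
- A two-arm regression leaves 24 − 4 = 20 residual degrees of freedom, against the 66 behind the three-arm interaction test.
- aIST vs SOC and dIST vs SOC would be adjusted for different sets of measurements.
- The estimate relies on an effort-dependent preoperative MIP measured after randomization, as the planned contrast already does.
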